## Abstract

**Background:**

Controlling blood pressure with drugs is a key aspect of cardiovascular disease prevention, but until recently has been the sole preserve of health professionals. Self-management of hypertension is an under researched area in which potential benefits for both patients and professionals are great.

**Methods and design:**

The telemonitoring and self-management in hypertension trial (TASMINH2) will be a primary care based randomised controlled trial with embedded economic and qualitative analyses in order to evaluate the costs and effects of increasing patient involvement in blood pressure management, specifically with respect to home monitoring and self titration of antihypertensive medication compared to usual care. Provision of remote monitoring results to participating practices will ensure that practice staff are able to engage with self management and provide assistance where required. 478 patients will be recruited from general practices in the West Midlands, which is sufficient to detect clinically significant differences in systolic blood pressure between self-management and usual care of 5 mmHg with 90% power. Patients will be excluded if they demonstrate an inability to self monitor, their blood pressure is below 140/90 or above 200/100, they are on three or more antihypertensive medications, have a terminal disease or their blood pressure is not managed by their general practitioner.

The primary end point is change in mean systolic blood pressure (mmHg) between baseline and each follow up point (6 months and 12 months). Secondary outcomes will include change in mean diastolic blood pressure, costs, adverse events, health behaviours, illness perceptions, beliefs about medication, medication compliance and anxiety. Modelling will evaluate the impact of costs and effects on a system wide basis. The qualitative analysis will draw upon the views of users, informal carers and professionals regarding the acceptability of self-management and prerequisites for future widespread implementation should the trial show this approach to be efficacious.

**Discussion:**

The TASMINH2 trial will provide important new evidence regarding the costs and effects of self monitoring with telemonitoring in a representative primary care hypertensive population.

**Trial Registration:**

ISRCTN17585681

## Background

National and international surveys have found that despite some recent improvements, the blood pressure of many people with hypertension remains poorly controlled. [1,2] This is despite evidence that reduction to <140/90 mmHg is achievable and results in important benefits in terms of morbidity and mortality.[3] Adequate blood pressure control is a prerequisite if cardiovascular disease is to be reduced in line with recent UK policy targets.[4,5]

There are many potential reasons for sub-optimal blood pressure control. Hypertension is largely asymptomatic with little biological feedback to patients in terms of blood pressure control. Treatment is generally life long and may be associated with dose related side effects. It is therefore perhaps not surprising that adherence to antihypertensive medication is often poor with around half of hypertensive patients discontinuing new prescriptions for antihypertensive drugs in the first six months.[6]

It is not simply a question of motivating patients. Research in UK general practice has shown a lack of professional action in the presence of high recorded blood pressures along with a reluctance to prescribe for isolated systolic hypertension.[7] Fear of side effects may be one reason for this inaction although modern treatment trials have shown relatively modest levels of side effects.[2] Workload in primary care has been cited as another reason for poor performance, with the average practice having to provide care for several hundred people with hypertension.[8] Novel approaches for the management of high blood pressure are therefore required.

There is good evidence for both pharmacological and non-pharmacological interventions.[9] The advent of accurate and easy to use automated sphygmomanometers means that blood pressure measurement need no longer be confined to professionals. Health behaviour models suggest that increased patient involvement in disease management will result in cues to action and increased self-efficacy with improved adherence to treatment and beneficial changes in other health behaviours such as in diet and exercise.[10]

Four previous randomised studies have evaluated the efficacy of telemonitoring in conjunction with self-monitoring of hypertension and other interventions but none have been adequately powered, followed up for more than six months, or set in the UK. [11-14](Table 1) Friedman's 1996 study randomised 267 hypertensive patients under the care of community physicians to self-monitoring with an interactive telephone reporting system or usual care. Intervention patients measured their own blood pressure on a weekly basis and reported the results via the "TLC" computerised telephone system. [11] This system, as well as recording blood pressure, provided automated feedback to the subject before transmitting results to an individual's physician. The authors found a significant benefit from the intervention in terms of diastolic blood pressure once adjusted for baseline differences between the groups. No such difference was seen for systolic blood pressure. Roger and colleagues studied 121 hypertensive people recruited from a hospital clinic. [12] Automated blood pressure readings were transmitted to the study centre via telephone. The intervention group had slightly reduced (3 mmHg) mean arterial pressure as measured by twenty-four hour blood pressure monitoring which remained significant after adjustments for baseline differences between groups. The final two trials by Mehos (34 patients) [13] and Artinian (26 patients) [14] were too small to draw conclusions from other than the fact that community based telemonitoring of blood pressure is feasible in a range of settings.

**Table 1 T1:** Summary of randomised studies evaluating self-monitoring with telemonitoring or self-management

**Study**	**Number of subjects** **Mean age** **Length of follow up**	**Type & frequency of BP self measurement**	**Frequency of other input (either as co-intervention or outcome measurement)**	**Was physician adjusting medication aware of self measurement readings**	**Outcome measurement**	**Outcome of study**
Friedman 1996 US [11]	267 patients under care of community physicians Age 77 6 months	Automated Weekly (?upper arm)	Self report of BP, adherence etc via computerised telephone system (TLC) on a weekly basis with automated feedback	"TLC" data transmitted to patient's own physician	BP measured on home visit; protocol for measurement not clear if blinded	Small drop in DBP only after adjustment (mean adjusted DBP change 5.2 mmHg vs 0.8 mmHg, No CIs, p = 0.02)
Mehos [13] 2000 US	36 primary care patients with poorly controlled hypertension 59 years 6 months	Manual electronic Daily Upper arm	Monthly telephone calls to coordinate treatment changes All received counselling on ht rx and lifestyle	Yes	not clear if blinded	No CI s or p quoted
Rogers [12] 2001 US	121 hypertensive patients from hospital clinic 61 years At least 8 weeks	Automated 3 days per week (? upper arm)	Transmission of results of BP down phone line Monthly reports to patient and physician electronically generated	Yes	Main outcome ambulatory BP monitoring pre and post intervention which physicians were blinded to	Reduction in MAP of 3 mmHg, (no CI, p = 0.013)
Artinian [14] 2001 US	26 African American with hypertension attending a family community centre	Automated At least 3 days per week Upper arm	Transmission of BP results down phone line each Friday with automated feedback to patients Additional feedback via study nurse	Yes	Clinic measurement before and after measured by blinded investigator	Pilot study: no formal comparison of between group BP drop.
Zarnke [15] 1997 Canada	31 hypertensive primary care patients 55 years 8 weeks	Electronic Twice daily (?upper arm)	Self directed adjustment of medication Self help advice to all	Yes if consulted when patient had already tried to change treatment	Mercury sphyg; not clear if blinded but externally measured. Also ambulatory BP	Intervention group had lower mean ambulatory MAP.(-0.95 vs +1.9 mmHg, No CI, p = 0.039)

A further study [15] by Zarnke and colleagues in Canada has evaluated self-management of hypertension (Table 1). 31 patients with hypertension were randomised between usual care and self-directed adjustment of medication using a fixed set of antihypertensive medication. Follow-up after eight weeks showed a small drop in mean arterial pressure in the intervention group compared to control.

These studies have been combined with other self-monitoring work in two systematic reviews. [16,17] These showed that, in common with other non-pharmacological interventions, self-monitoring, with or without telemonitoring, has a modest effect on blood pressure. One subsequent randomised study has evaluated self-monitoring in a UK primary care setting. [18] This work by our group showed that people with hypertension were able and willing to self-monitor blood pressure, and that the small reductions in blood pressure were probably mediated through lifestyle changes and that self-monitoring is cost effective.

The studies discussed above have all been quantitative studies and there has been very limited exploration of patients' views of self-monitoring. [19,20] There is currently no information on potential issues arising from self-management of hypertension from the perspective of patients, carers or health care providers.

Therefore, the TASMINH2 study is an extension of our previous work, expanding the intervention from self monitoring to self management to include not only self monitoring of blood pressure, but telemonitoring and self titration of antihypertensive medication, with the expectation that this will result in larger reductions of blood pressure.

## Methods

### Study Aims, Research Questions, and Outcomes

The primary aim of TASMINH2 is to compare self management with usual care in the control of hypertension. The trial has four main research questions:

1) Does self-management with telemonitoring and titration of antihypertensive medication by people with poorly controlled hypertension result in better control of blood pressure?

2) Is self-management with telemonitoring and titration of antihypertensive medication by people with poorly controlled hypertension cost effective?

3) Is self-management with telemonitoring and titration of antihypertensive medication achievable in routine practice and is it acceptable to patients?

4) What are the views and experiences of patients, informal carers and healthcare professionals of self-management with telemonitoring and titration of antihypertensive medication?

The primary outcome of the trial will be the change in mean systolic blood pressure (mmHg) between baseline and each follow up point (6 months and 12 months), measured in the surgery by the research team. Additional secondary outcomes will include change in mean diastolic blood pressure, adverse events (side effects, anxiety), health behaviours, illness perceptions, beliefs about medication, medication compliance, patient satisfaction, costs and reasons for non-participation as well as the qualitative analysis and health economic modelling beyond the trial outcomes.

### Study Design and Setting

TASMINH2 is a primary care based, unblinded, randomised controlled trial with embedded economic and qualitative analyses in order to evaluate the costs and effects of increasing patient involvement in blood pressure management.

### Ethical considerations

Full ethical approval for this trial has been obtained from Sandwell and West Birmingham local ethics committee (reference; 05/Q2709/103), whilst site specific ethical approval and R & D approval was obtained from the relevant local ethics committees and Primary Care Trusts. A trial steering group will monitor study progress.

### Trial Interventions

Usual care will consist of the participant seeing their General Practitioner (GP) (Family Physician) and/or nurse periodically for blood pressure measurement and/or adjustment of medication at the discretion of the GP.

Self-management will consist of self-monitoring of blood pressure with electronic transmission of readings, and self titration of medication dependant on the self-monitoring readings.

#### Blood pressure self-monitoring

Participants will be trained to monitor their blood pressure using an automated electronic sphygmomanometer. Home readings will be transmitted to the research team via the telemonitoring system. Patients will self-monitor blood pressure daily for the first week of each month of the study. They will be provided with a guideline that contains simple colour coded instructions. Very high or very low readings will require checking by the participant's practice. Four or more above target readings in two consecutive months will require a change in medication. Below target readings will simply require further monitoring the following month.

#### Target Blood Pressure

Target blood pressures will be based on the NICE hypertension guideline with adjustment of 10/5 mmHg as recommended by the British Hypertension Society to reflect home as compared to office readings. [21,22] People without diabetes will have a home target of ≤130/85 mmHg. People with diabetes or CKD stage 3–5 will have target blood pressures of ≤130/75 mmHg to take into account the lower NICE recommendations.

#### Telemonitoring

Participants will be trained in the use of the telemonitoring equipment at baseline and home visits (practical technical help) will be available if required to set up equipment. The equipment consists of a standard validated automated electronic sphygmomanometer (Omron 705-IT) with a modem for telemonitoring (Melexis I-modem). Blood pressure data (including time and date) will be transferred to the research team from the memory of the electronic sphygmomanometer via an internet connection. Practices will receive summary data from the research team once each month, by report to allow incorporation into clinical records systems. In addition, blood pressure recordings will also be available to patients via a secure internet site which will summarise individual patient's monitoring results.

#### Self-titration of medication

Each participant will be given an individually tailored two step self management algorithm through which to adjust medication according to measured blood pressure. The choice of medication changes will be decided in conjunction with their own GP. Each step will represent a single medication change (additional medication or increased dose) that will be made following raised readings in two consecutive months. Medication choice will remain that of the GP who will be provided with a copy of the NICE hypertension management algorithm to aid choice of medication. If patients have used both steps of their self-management algorithm they will return to the GP and a new two step plan will be devised. As the study will last for 12 months, patients will not require any more than two such management plans. Any additional monitoring (for instance blood tests or urinalysis) will be the responsibility, and at the discretion, of the GP.

### Non-Participation

Included with the letter of invitation to take part in the trial, will be a form for people to voluntarily return should they wish to decline the invitation. As well as asking for their reasons for wishing to decline, this form will also seek permission to send a further questionnaire and/or gain their permission for the research team to have access to their medical records. The further questionnaire will be similar to that which will be used in the research clinics/follow-up sessions with people enrolled in the study. Following-up those who decline to take part will provide useful information regarding the generalisability of the trial results, as well as providing a greater insight into the reasons why people may not wish to self-manage their hypertension.

### Study Population, Sampling and Recruitment Procedure

The study population will comprise of people with poorly controlled treated hypertension managed in primary care. Eligibility criteria will be age between 35–85, treated hypertension, and blood pressure greater than 140/90. Exclusion criteria will be inability to self-monitor (including diagnosis of dementia, score of >10 on short orientation memory concentration test), postural hypotension (systolic blood pressure drop >20 mmHg), more than two antihypertensive medications, terminal disease, and blood pressure not managed by their GP. (see Table 2)

**Table 2 T2:** Inclusion and Exclusion Criteria

**Inclusion Criteria**
Age between 35–85
Treated hypertension (diagnostic code for hypertension plus prescription for antihypertensive medication)
Blood pressure greater than 140/90 at baseline
Willingness to self monitor and self manage
**Exclusion Criteria**
Inability to self monitor (including diagnosis of dementia, score of >10 on short orientation memory concentration test)
Current prescription for more than two antihypertensive medications
Terminal disease
Blood pressure not managed by their General Practitioner
Postural Drop > 20 mmHg systolic

Eligible patients will be identified from around 15 general practices in the West Midlands area drawn from the Midlands Research Practices Consortium (MidReC).[23] A member of the research team will conduct a practice-based computer search to identify patients that fulfil the eligibility criteria. General Practitioners will be asked to check these computer generated lists to remove people who are known to have terminal illness, those not managed by the GP or who are thought by the GP to be unsuitable for the study. Previous experience from the TASMINH trial suggests that around 25–30% of people receiving treatment for hypertension will take part in a study such as that proposed.[18] We plan to recruit patients from each practice over a 2–3 week period before moving on to the next practice. Assuming 40 patients per practice are recruited then around 50 will need to be screened and so at least 200 will need to be invited.

Participants who withdraw from the trial will not be replaced, but asked if they are prepared to continue to attend follow-up clinics. Analysis will be by intention to treat.

### Randomisation

Randomisation of patients with uncontrolled hypertension will be to either usual care or self-management of their hypertension and will take place centrally via telephone or internet using the process of minimisation taking into account practice, sex, diabetic/chronic kidney disease status, baseline blood pressure and age.

### Study Clinics and Flow through Study

At baseline all patients will attend a clinic at which the study will be explained, informed consent gained and questionnaires regarding demographics, past medical history, self-efficacy and attitudinal compliance will be completed (Table 3). Measurement of blood pressure and BMI will also be performed and baseline economic data collected. Patients will be randomised to either usual care or self-management. People randomised to usual care will be asked to book an appointment approximately one week later for a medication review with their usual GP. People randomised to self-management will be asked to book an appointment for a group training session where they will be trained to use an electronic sphygmomanometer and the telemonitoring system. After the group training session, patients will be asked to practice at home using their blood pressure monitors and telemonitoring system, and return approximately one week later for an individual training session which will cover the self-titration part of the intervention. If necessary a third training session will be included for additional support. Following satisfactory training (assessed by one of the research team), patients will be asked to make an appointment with their GP to establish a two step management plan for any potential medication changes. Patients not judged to be able to self-manage will be given the option to self-monitor alone.

**Table 3 T3:** Data Collection at Study Clinics

Baseline Only:
1. Demographic questions; including race, occupation, marital status, employment, education,
2. Length of hypertension
3. Past medical history
4. Contraindications/intolerance to antihypertensives
5. Short orientation memory concentration test[29]
6. Height
7. Current self monitoring behaviour

Baseline and subsequent follow up
1. Current antihypertensive medications
2. Symptom section of the Illness Perception Questionnaire [30]
3. Weight
4. New medical history (in last 6 months)
5. Preference for blood pressure measurement methods
6. Beliefs About Medicines Questionnaire [31]
7. Medication Compliance sub-scale of the Hill-Bone Compliance to High Blood Pressure Medication Scale [32]
8. Short-form of the State-Trait Anxiety inventory [33]
9. EQ5-D [34]
10. Godin's Exercise Questionnaire [35]
11. Questions on smoking, alcohol consumption and salt intake
12. Economic data (referrals, consultations, resource use, willingness to pay)
13. Blood Pressure (sitting plus standing at baseline only)

All patients will be asked to attend two follow-up clinics; one at 6 months and one at 12 months. Each clinic will be timetabled for approximately half an hour, in which time patients will have their blood pressure measured by the research team using a validated automated electronic sphygmomanometer, and will be asked to complete a questionnaire similar to that completed at baseline. Additionally, the research team will check that patients in the intervention arm are using the blood pressure monitors correctly. This is shown in Figure 1.

**Figure 1 F1:**
[figure not shown]
**Flow through the study**.

### Sample size considerations

A sample size of 191 people per group is required for 90% power assuming a standard deviation of 15 mmHg and a difference in reduction of blood pressure of at least 5 mmHg between intervention and control groups. A reduction of 5 mmHg systolic blood pressure is plausible in comparison with other studies of self-monitoring of blood pressure and should result in around 19% reduction in stroke risk. Clinic measurements are used as the primary end point as these are comparable to most treatment studies. Based on the drop out rate from the initial TASMINH self monitoring trial, and taking into account the additional requirements of this trial, a 20% drop out rate during follow-up is assumed, meaning that a sample size of 239 per group will need to be randomised, i.e., 478 people. We estimate that between 10–15 practices will be required i.e., 35–50 patients per practice.

### Statistical Analysis

Analysis will be on an intention to treat basis for complete cases. A sensitivity analysis will examine the potential effect of missing data. This will include replacement of missing data by the most recent previous data or by the mean of the series. The principal analysis will be performed using both raw and adjusted data and will be performed at the end of the trial after all data has been collected. The primary analysis will be using general linear modelling (GLM) to compare intervention and control systolic blood pressure at follow-up adjusting for baseline blood pressure, practice (as a random effect), diabetic or CKD status and sex. Planned sub group analyses will be of diabetic vs non-diabetic patients, older vs younger (65 as threshold), males vs females, better controlled at baseline vs worse controlled at baseline (> vs < 155 mmHg systolic).

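### Age is used to balance the allocation but is left out of the primary model; if age is prognostic, a little precision is lost (minor)

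*Protocol article*

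**What the plan says.** The Randomisation section of the protocol article allocates patients centrally by minimisation on "practice, sex, diabetic/chronic kidney disease status, baseline blood pressure and age".

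The Statistical Analysis section specifies a general linear model for systolic pressure at follow-up, "adjusting for baseline blood pressure, practice (as a random effect), diabetic or CKD status and sex". The principal analysis is to be run on both raw and adjusted data, so this list defines the adjusted analysis.

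In the analysis section age appears only as a planned subgroup split, "older vs younger (65 as threshold"). The enrolled range is wide: "Age between 35–85".

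The sample size section states: "A sample size of 191 people per group is required for 90% power". Its inputs are an SD of 15 mmHg and a 5 mmHg gap between the arms in the fall in pressure. It takes no credit for covariate adjustment.

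**The concern.** Four of the five minimisation factors are carried into the primary model and one is dropped without comment. The article does not leave the covariates to a later document. It gives an explicit list, and that list does not match the allocation scheme described in the same article.

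Minimisation makes the arms more alike on age than simple randomisation would. If age predicts the outcome, the treatment estimate then varies less from trial to trial than a model without age assumes, because that model still counts age's contribution as residual noise. The reported standard error is too large, the confidence interval is wider than it need be, and the test is slightly conservative. What is at stake is precision in the primary comparison, not its validity.

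**Working it through.** **Inputs from the article.** 191 per group, 90% power, SD 15 mmHg, difference 5 mmHg, 20% drop-out, 478 randomised.

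**Assumptions.**
- Two-sided 5% test. The level is not stated, but a one-sided 5% test would need only 155 per group.
- 15 mmHg is the residual SD with age omitted.
- r is the partial correlation of age with follow-up systolic pressure, given the other covariates. The article gives no value; 0.1 to 0.3 is used, with 0 as the reference.
- Age is perfectly balanced between arms. This makes the standard-error and type I error figures limits.

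**Step 1: reproduce the plan's figure.** n = 2 × 15² × (1.960 + 1.282)² / 5² = 189.1, which rounds up to 190 per group. The t-based solution is 190.1, which rounds up to 191, as stated. With 20% drop-out, 191 / 0.8 = 238.75, so 239 per group and 478 in total. Power at 191 per group is 90.3%.

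**Step 2: standard errors.** Without age, the model SE = 15 × √(2/191) = 1.535 mmHg. With age, SE = 1.535 × √(1 − r²). The ratio of the two is 1/√(1 − r²).

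**Step 3: true level with age omitted.** 2 × [1 − Φ(1.96/√(1 − r²))]. The true sampling SE is the smaller one, but the test uses the larger.

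**Step 4: power.** Let SE₁ = 1.535 × √(1 − r²).
- Age omitted: Φ(5/SE₁ − 1.96/√(1 − r²)).
- Age included: Φ(5/SE₁ − 1.96).

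At r = 0.3, SE₁ = 1.464 and 5/SE₁ = 3.415. The effective critical value with age omitted is 1.96/0.954 = 2.055. Power is therefore Φ(1.360) = 91.3% without age and Φ(1.455) = 92.7% with it.

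| r | SE too large by | True level, age omitted | Power, age omitted | Power, age included | Difference (points) |
|---|---|---|---|---|---|
| 0 | 0% | 5.0% | 90.3% | 90.3% | 0 |
| 0.1 | 0.5% | 4.9% | 90.4% | 90.6% | 0.2 |
| 0.2 | 2.1% | 4.6% | 90.7% | 91.4% | 0.7 |
| 0.3 | 4.8% | 4.0% | 91.3% | 92.7% | 1.4 |

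Differences are taken before rounding.

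**Step 5: the loss in patients.** Find the group size at which the model with age has the same power as the model without age at 191. This is 189.9, 186.4 and 180.6 per group for r = 0.1, 0.2 and 0.3. Over both arms the loss is about 2, 9 and 21 of the 382 completers.

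**Step 6: simulation check.** Minimisation on all five factors was simulated with 382 patients, 12 practices entered as fixed effects and 3,000 trials per scenario.
- With age explaining 5% of residual variance (r about 0.22), the model SE without age was 1.54 against an empirical 1.48 to 1.50. Power was 90.8% without age and 91.9% with it.
- At 10% (r about 0.32), the model SE was 1.54 against about 1.47. Power was 91.0% and 93.3%.
- With age non-prognostic, the two models performed alike.

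Simulated rejection rates under the null ranged from 4.3% to 5.9%. With 3,000 trials their Monte Carlo error is about 0.4 points (√(0.05 × 0.95/3000)), so they are too noisy to confirm the small shifts in level.

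**The case against.** The strongest objection is that nothing in the article shows age to be prognostic once baseline pressure, sex and diabetes/CKD status are in the model. If it is not, the omission costs nothing. This stands: the mismatch is certain, but its consequence is conditional. The age subgroup does not settle the matter, because planning to test whether age modifies the treatment effect is not evidence that age predicts the outcome.

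A second objection is that the figures assume perfect balance on age. The article does not say how age enters the minimisation, and five factors including 10 to 15 practices leave some imbalance. Balance among those randomised also need not carry over fully to the complete cases analysed. This stands too, so the standard-error and level figures are upper limits on the distortion for a given r.

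A third objection concerns the size of the loss. A reader might take 382 × r², or 4 to 34 completers, as the power given away. That quantity measures the widening of the reported interval. When age is balanced, the true sampling variance has already fallen and only the critical value is too large, so the power loss is the smaller 2 to 21.

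None of this supplies a reason for omitting age. The covariate list is explicit, so condensation for a journal does not explain the gap.

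**Conclusion.** The point holds as a minor one. The primary model omits a minimisation factor without explanation. Given r between 0.1 and 0.3 and good balance on age, the cost is a standard error up to 0.5% to 4.8% too large and 0.2 to 1.4 points of power; at r = 0 there is none.

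A reader might infer that the trial is underpowered, that the estimate is biased or that the test is invalid. The documents do not support any of these. The 191 per group was computed without credit for covariates, and on these assumptions power with age omitted stays at or above 90.3%. Leaving out a balanced covariate does not bias the difference in means, and the error in the level is towards conservatism. Nor can it be said outright that the standard error is overstated, since that rests on a correlation the article does not give.

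**What to change.** Add age to the covariates of the primary model in the Statistical Analysis section, so that the list is baseline systolic pressure, age, sex, diabetes/CKD status and practice. A continuous term is preferable because it uses the full 35 to 85 range, but the functional form is a matter of choice and should be stated. If age is left out on purpose, give the reason.

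The cost is one word in the text and, for a linear term, one degree of freedom. Age is already needed for eligibility and allocation, so no further data are required. The change should be made before outcome data are examined, because adding a covariate later could look data-driven. The sample size need not change.
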